## Abstract

**Background:**

Since there is a shift from eating lunch at home to eating lunch at primary schools in the Netherlands, providing a school lunch may be an important opportunity to improve the diet quality of Dutch children. Therefore, the aim of this Healthy School Lunch project is to encourage healthy eating behavior of children at primary schools by offering a healthy school lunch, based on the guidelines for a healthy diet. In this study, two research questions will be addressed. The first research question is: What and how much do children consume from a self-served school lunch and how do they evaluate the lunch? The second research question is: Do children compensate healthier school lunches by eating less healthy outside school hours? The purpose of this paper is to report the rationale and study design of this study.

**Methods:**

In the Healthy School Lunch project children in grades 5–8 (aged 8–12 years) of three primary schools in the Netherlands will receive a healthy school lunch for a 6-month period. To answer research question 1, lunch consumption data will be collected at baseline and again at 3- and 6-months. This will be measured with lunch photos and questionnaires among children. To answer the second research question, a quasi-experimental, pre-test post-test intervention-comparison group design (3 intervention schools and 3 comparison schools) will be carried out. Potential compensation effects will be measured with a single brief questionnaire among parents at the three intervention and three comparison schools at month 6 of the lunch period. The school lunch will also be evaluated by parents (discussion groups) and teachers and support staff (brief questionnaires).

**Discussion:**

Results of this study will provide valuable information to influence future school lunch interventions and policies.

**Trial registration:**

This study is registered at the Netherlands trial register (NTR): trialregister.nl, Trial NL7402 (NTR7618), registered retrospectively at 2018-11-13.

## Background

Encouraging children to eat healthy is a high priority in public health globally. This is of crucial importance so that children maintain a healthy body weight and stay physically fit. Children with a healthy body weight have a greater chance of staying that way during adulthood. Moreover, a healthy body weight reduces the risk of premature onset of illnesses later in life, including diabetes type 2 and heart diseases [1, 2].

The most important contributor to a healthy body weight is an appropriate dietary intake. Children living in the Netherlands consume a dietary pattern high in foods and beverages with high levels of sugar, salt and saturated fat such as sugar-sweetened beverages, fried foods and sweet snacks [3]. Dutch children have one of the highest intakes of sugar-sweetened beverages in Europe [4]. Especially this high intake of sugar-sweetened beverages is concerning because this is related to overweight and obesity [5]. In the Netherlands, there were 13.1% of 4–11 year old children with overweight, and 3.3% with obesity in 2017 [6]. Furthermore, the diet of Dutch children is relatively low in healthy foods like fruit, vegetables, fish and whole grain products [7]. For example, 4–12 year old children eat on average 74 g of vegetables per day while the recommended daily intake is 125 to 175 g per day or more. Ninety-five percent of the children in this age group eat less than the daily recommended amount of vegetables [7]. Specifically children with a low social economic position (SEP) are likely to consume more energy-dense foods and beverages high in sugar, salt and saturated fat compared to children from middle- and high SEP groups [8]. This was confirmed by a recent study that concluded that having a lower SEP was independently negatively associated with healthier diet among 5-year old children living in the Netherlands [9].

Almost all children spend a substantial part of their time at school, making it a suitable place for health promotion [10]. In the Netherlands, they consume part of their daily energy intake during this time by eating their lunch and morning snacks at school. We recently investigated the content and quality of packed lunches of Dutch school children which they brought from home. We observed that a typical lunch of Dutch school children consists of a sandwich with a sweet or savory topping and milk or a sugar-sweetened beverage as drink. Children consumed very little fruit or vegetables during lunch. Furthermore, children who stayed at school during lunch consumed statistically significantly more sugar-sweetened beverages compared to children who ate their lunch at home [11].

Unlike countries such as Norway, Sweden, France, the UK or the USA, there is no practice of lunch school meal programs in the Netherlands [12]. Dutch primary school children bring their own packed lunches from home or go home for lunch. However, there has been a transition towards a ‘continuous schedule’ in the last years, where children do not go home for lunch and thus eat their packed lunch at school [13]. These changes in the Netherlands create an opportunity to provide a healthy school lunch since all children eat their lunch at school. An additional advantage is that in this way children from all socio-economic backgrounds can be reached since it is known that groups with a lower SEP are usually more difficult to reach for health promotion programs. For these reasons, the school setting provides a good opportunity to reduce socioeconomic inequalities in the diets of children. This was confirmed by results from a previous randomized controlled trial performed among Danish 8–11 year old children. Andersen et al. observed that overall dietary intake was improved at the food and nutrient levels when children’s habitual packed lunches were replaced by school meals for a three-month period. For example, the intake of vegetables increased with 16% in the intervention period compared to the control period [14].

Overall, children’s diet is an important contributor to their development and growth and overall health in later life. Eating habits that are adopted in childhood often persevere into adulthood [15] and therefore it is important to teach and stimulate healthy eating practices as early as possible. Therefore, the aim of this study is to encourage healthy eating during lunch of children in the primary school setting by offering a healthy school lunch, based on the Dutch guidelines for a healthy diet. In this study, two research questions will be addressed. The first research question is: What, how much and how healthy do children consume from a self-served school lunch and how do they evaluate the lunch? The second research question is: Do children compensate healthier school meals by eating less healthy outside school hours?

## Methods

### Study design

In the Healthy School Lunch project children in grades 5–8 (aged 8–12 years) of three primary schools in the Netherlands will receive a healthy school lunch for a 6-month period (November 2018 to April 2019). The development of this healthy school lunch is guided by a study among parents and children about desired school lunch concepts [16, 17]. Important to note is that in the Netherlands, it is very common for children to take all their foods and drinks from home (morning snack and lunch). There is no opportunity to buy food or drinks at primary school and there is no national subsidized school lunch program which offers school meals. Most primary schools in the Netherlands report to have a written food policy (e.g. on what is allowed to bring) although there is no legal obligation to do so [18].

To answer research question 1, we will collect lunch consumption data by means of pictures. All intervention group children will have to complete an initial baseline measurement in the situation where they still bring their own packed lunch. They will also have to complete a second and third follow-up questionnaire at month 3 half-way and month 6 at the end of the period in which a healthy school lunch will be provided.

To answer the second research question, a quasi-experimental, intervention-comparison group design (3 intervention schools and 3 comparison schools) will be carried out. There will be no randomization of the intervention and comparison schools, as the schools had to fully agree and decide on their participation beforehand, which required consent from their stakeholders (teachers, parents, support staff). Potential compensation effects will be measured with a single brief questionnaire among parents both at the three intervention schools and at the three comparison schools at month 6 of the lunch period. The school lunch will also be evaluated by parents (discussion groups) and teachers and support staff (brief questionnaire).

Schools do not receive funding to use for implementing the school lunch themselves. The expenses for ordering lunch products will be paid by the project fund. Parents will be informed about the study by means of a letter and informational meetings. A voluntary financial contribution for the costs of the lunch will be asked from parents, although it will not be registered whether and how much individual parents will pay. A small box will be put in each classroom in which children can put their financial contribution.

Active written parental consent will be obtained for all children before the study starts. Children also give verbal consent for making a photograph of their lunch. Parents may request at any time to withdraw their children from the study. The study has been approved by the Social Ethical Committee of Wageningen University, the Netherlands and is registered at the Netherlands trial register (NTR): www.trialregister.nl.

### Recruitment

A convenience sample of three primary schools agreed to participate in the intervention condition. Initial contact was established with more than 20 schools in different parts of the Netherlands, particularly focused on Amsterdam and Ede. Schools were contacted by members of the research team to recruit them for the study. In addition, a presentation was conducted for interested school personnel at a regional meeting for school directors. Recruitment of schools was based on pragmatic reasons. Inclusion criterion was having a continuous time schedule, where children lunch at school.

A power calculation was conducted to determine the sample size necessary to detect changes in the primary outcome variable ‘vegetable consumption’. Only 6.7% of Dutch primary school children eat some vegetables at school during lunch [11]. We calculated the required sample size with a study group incidence of 13.4% of children eating some vegetables (doubling the population incidence of 6.7%). This is a conservative estimate, as for each participating child 50 g of vegetables will be available each day. In the case of doubling the population prevalence, 134 children would be needed in the study sample to reach a required power of 0.8, when the statistical analysis will be performed at the 2-tailed alpha (0.05). This calculation is made using the sample size calculator ClinCalc [19]. To account for the clustered nature of the data (classes in three schools), the need for a proper process evaluation and potential dropouts, more participants are needed.

Schools were situated in the capital of the Netherlands Amsterdam and in two small cities, i.e. Lunteren and Vlaardingen (10.000–100.000 inhabitants). Two of the three schools are situated in a district characterized by residents with a lower SEP (Amsterdam and Vlaardingen) and one in a semi-rural town with children of parents with a relatively high SEP (Lunteren). Comparison schools were recruited to match these SEP levels. All children of grades 5 till 8 were invited to participate in the study. Children of grades 1 to 4 were not invited. This was done given budget constraints and we expected that older children would be better able to reflect on their experiences in the questionnaire. Children and parents who decided to join the lunch after the start will also be enrolled. Consequently, data at baseline can be missing for these children. Letters will be sent to parents to explain the study and school lunch. At each school, information meetings will be set up to inform all parents and children. All parents of children that participate will be send a letter after about three months with an invitation to give feedback about the school lunch. This evaluation is not part of the measures, but will be used to adapt and improve the intervention if necessary.

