### Data analysis

#### Consumption and evaluation of lunch by children

The unit of analysis will be the child. The primary outcome measures of this study is the food and drink consumption of the children during lunch, which is measured by analyzing photographs of the lunch of each child. Vegetable portion size in grams will be estimated based on the pictures and observation forms. Bread will be reported in type of bread and slices, crackers and fruit in pieces and drinks in milliliters. Of all products, intake will be assessed by subtracting the portion after from the portion before and tested for statistically significant differences. Important outcomes will be the incidence of children consuming a particular product. Success of the intervention will be indicated by at least 50% of the children consuming at least a portion of 25 g of vegetables during lunch.

The number of different products per lunch will be calculated. Next, the share of healthier ‘Wheel of Five’ products consumed will be plotted and compared across time using chi-square analyses and correlations. Acceptability of the school lunch is assessed by the questionnaire item ‘the lunch was tasty’ assessed at T1 and T2. Adequate acceptability will be indicated by 75% of the children reporting a mean rating of three or higher.

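### The 134 children for 80% power come from a one-sample test against a fixed 6.7%, not from the before-after comparison that the study makes

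*Protocol article*

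**What the plan says.** The power calculation is in the Recruitment section of the protocol article. Its purpose is given as "to determine the sample size necessary to detect changes in the primary outcome variable", namely vegetable consumption. The reference rate comes from a cited earlier study: "Only 6.7% of Dutch primary school children eat some vegetables at school during lunch". Against it the authors set "a study group incidence of 13.4% of children eating some vegetables", a doubling that they call conservative. With two-sided alpha 0.05, the result is that "134 children would be needed in the study sample to reach a required power of 0.8". The paragraph ends by naming the clustering of classes in three schools and adding "the need for a proper process evaluation and potential dropouts, more participants are needed". No enlarged number follows.

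The design for research question 1 is a before-after comparison. Under Study design, "All intervention group children will have to complete an initial baseline measurement" while they still bring a packed lunch. Under Outcome measures, the lunch measurement is repeated at T1 (3 months) and T2 (6 months). Under Data analysis, product intake is to be tested for differences without naming a test, and the share of Wheel of Five "products consumed will be plotted and compared across time using chi-square analyses and correlations". The article describes no test of the study children against the external 6.7%.

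**The concern.** A sample size for detecting change has to allow for sampling error at both time points and for the correlation between them. Here the only comparator in the calculation is an outside rate treated as exactly known. If 134 comes from that simpler problem, the stated power of 0.8 does not apply to a comparison of follow-up with the children's own baseline.

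This is the only power statement in the article, and it concerns the named primary variable. A reader who accepts it could take a non-significant change as good evidence against a doubling of vegetable eating, when the study might have had little better than an even chance of detecting one.

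**Working it through.** **Inputs from the article (Recruitment).** p0 = 0.067, p1 = 0.134, difference d = 0.067, two-sided alpha 0.05 (z = 1.960), power 0.80 (z = 0.8416), n = 134. The article gives no within-child correlation, intraclass correlation or class size.

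**Step 1: reproduce 134.** One-sample test against a fixed p0:

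n = [1.960·√(p0(1−p0)) + 0.8416·√(p1(1−p1))]² / d² = (0.4900 + 0.2867)² / 0.067² = 0.6033 / 0.004489 = 134.4.

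Power at n = 134 is 79.9%. Other readings do not give 134: the one-sided version gives 109, and two independent proportions give 315 per group (345 with continuity correction).

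**Step 2: two time points treated as independent.** With mean proportion 0.1005, the null variance is 2 × 0.1005 × 0.8995 = 0.1808 and the alternative variance is p0(1−p0) + p1(1−p1) = 0.1786.

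- n for 80% = [1.960·√0.1808 + 0.8416·√0.1786]² / 0.067² = 315 per time point.
- Power at 134 per time point = Φ[(0.067·√134 − 1.960·√0.1808) / √0.1786] = 44.6%.

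**Step 3: paired comparison (McNemar, normal approximation).** Let φ be the within-child correlation of eating any vegetables at the two time points; this is an assumption. The proportion eating vegetables at both is p11 = p0·p1 + φ·√(p0(1−p0)p1(1−p1)) = 0.00898 + 0.08517φ. The discordant proportion is D = p0 + p1 − 2·p11. Then

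power = Φ[(d√n − 1.960·√D) / √(D − d²)] and n for 80% = [1.960·√D + 0.8416·√(D − d²)]² / d².

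| φ (assumed) | D | Power with 134 pairs | Pairs for 80% |
|---|---|---|---|
| 0 | 0.183 | 44% | 318 |
| 0.3 | 0.132 | 57% | 228 |
| 0.5 | 0.098 | 70% | 169 |
| 0.6 | 0.081 | 79% | 139 |
| 0.68 (maximum) | 0.067 | 86% | 115 |

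The maximum is √[p0(1−p1) / (p1(1−p0))] = 0.68, where no child who ate vegetables at baseline stops. Power reaches 80% at φ of about 0.62. There, about 0.5% of all children go from eating to not eating, which is roughly 8% of the baseline eaters (0.0052 / 0.067). The exact McNemar test is lower still: 36% at φ = 0 and 65% at φ = 0.5.

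**Step 4: a much larger effect.** For a rise from 6.7% to 50%, with 134 children at each of two independent time points and before clustering, power exceeds 99%.

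**The case against.** Four objections have force, and each blocks a stronger reading that a reader might infer.

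- **The test.** One might infer that the planned chi-square is the vegetable analysis and that its power is 45%. The Data analysis section attaches the chi-square to the share of Wheel of Five products and names no test for the proportion of children eating vegetables. The independent-time-point figure therefore shows what ignoring the pairing would give; it is not the power of a specified test.
- **Clustering.** One might infer that clustering was ignored. It was not: the Recruitment section says that clustering and dropout call for more than 134. A condensed article may leave the enlarged number to a fuller document. What stands is that any such increase is applied to a base from the wrong comparison.
- **The loss from clustering.** One might apply a conventional design effect and quote still lower power. The article gives neither an intraclass correlation nor a class size. In a before-after comparison within the same classes, stable class differences cancel, and the loss depends on how much the change varies between classes. No figure for that loss can be supported here.
- **Actual power.** One might conclude that the study is underpowered. The number enrolled is not given, all children in grades 5 to 8 of three schools were invited, and 134 is offered as a minimum. The authors call a doubling conservative, and their success criterion is that at least 50% of children eat at least 25 g. A rise of that order would be detected easily.

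None of this makes 0.8 the power for a doubling in a before-after comparison of 134 children. The 50% criterion is a success threshold for a stricter outcome, not the effect used in the calculation.

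**Conclusion.** The point holds as a mismatch between formula and design; the arithmetic itself is correct for the problem that it solves. The figure of 134 is valid for comparing independent children with a fixed 6.7%, and the article describes no such comparison. For the same effect measured against the children's own baseline, 134 pairs give 44% to 70% power if the within-child correlation lies between 0 and 0.5, before clustering. A power of 80% requires a correlation of about 0.62, close to the attainable limit of 0.68.

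The size rests on the article's own rates and alpha, on the assumed correlation range, and on the McNemar normal approximation. Usable pairs may also be fewer than children enrolled, because the Recruitment section admits late joiners whose baseline can be missing.

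**What to change.** Rewrite the power paragraph in three respects.

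1. State that 134 applies only to a one-sample comparison of independent children with a fixed 6.7%.
2. Withdraw the claim of power 0.8 for detecting changes.
3. Give the number of pairs, or the power, for the paired follow-up-versus-baseline comparison of the proportion eating vegetables, over a stated range of within-child correlation such as 0 to 0.5. Count only children with a baseline. Label any clustering allowance as an assumption about how much the change varies between classes.

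The cost is one paragraph and a small table. Data collection is already complete according to Study status, and no extra enrolment or change of analysis is asked for. The stated power for a doubling becomes less favourable; the ability to detect a much larger rise is not in question.

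### Late joiners can enter at three and six months without a baseline, and the comparison across time is not limited to children measured before the lunch began

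*Protocol article*

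**What the plan says.** All references are to the protocol article.

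- **Recruitment** allows entry once the lunch is running: "Children and parents who decided to join the lunch after the start will also be enrolled". It adds: "Consequently, data at baseline can be missing for these children".
- **Study design** describes a closed group. On consent: "Active written parental consent will be obtained for all children before the study starts". On measurement: "All intervention group children will have to complete an initial baseline measurement in the situation where they still bring their own packed lunch". The same section allows exit: "Parents may request at any time to withdraw their children from the study".
- **Data analysis, Consumption and evaluation of lunch by children** says the share of Wheel of Five products will be "compared across time using chi-square analyses and correlations". Intake of each product is to be tested for significant differences, with no test named. Success is "at least 50% of the children consuming at least a portion of 25 g of vegetables during lunch". Acceptability requires 75% of children to rate the lunch at three or higher, assessed at T1 and T2. The section does not say which children enter the time comparison or either percentage.

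**The concern.** Children measured at T0 are those enrolled before the lunch began. Children measured at T1 and T2 can be those who remain plus those who chose to enter later. If all available children are compared at each time point, part of any difference reflects a change in membership.

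This matters more here than in a controlled design. The comparison schools serve only the parent questionnaire on compensation, so research question 1 rests on before-and-after data from the intervention schools alone. An ordinary chi-square test across time treats the time points as independent groups and does nothing to separate the two sources of change. The subtraction described in the Data analysis section is between the start and end of a single lunch, not between T0 and a later visit, so it does not supply a within-child comparison over months. The limitations paragraph in the Discussion mentions other explanations for changed consumption in general, but not self-selected entry or exit.

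At stake are the T0 to T1/T2 change in vegetable eating and in healthier-product share and, in a different way, whose intake and liking count towards the 50% and 75% rules.

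**Working it through.** **1. The plan's own figure.** Inputs from Recruitment: p0 = 0.067, p1 = 0.134, two-sided alpha 0.05, power 0.80. For one sample against a fixed population rate:

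n = p0·q0·(1.960 + 0.842·√(p1·q1/(p0·q0)))² / (p1 − p0)² = 134.4

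This reproduces the stated 134 and is not disputed. It shows the effect the study is sized for: a rise from 6.7% to 13.4%.

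**2. Do the sections fit together?** Study design says every intervention child completes a packed-lunch baseline and that consent for all precedes the start. Recruitment enrols children after the start and says their baseline can be missing. Read literally, these cannot all hold.

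**3. How far can membership alone move a time comparison?** The documents give no joining or withdrawal rates, so every rate below is assumed and no child changes behaviour. Joiners are a fraction j of starters, with share pj eating vegetables:

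observed share = (0.067 + j·pj) / (1 + j)

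| j | pj | observed share |
|---|---|---|
| 10% | 13.4% | 0.0804/1.1 = 7.3% |
| 20% | 30% | 0.127/1.2 = 10.6% |
| 20% | 50% | 0.167/1.2 = 13.9% |
| 30% | 50% | 0.217/1.3 = 16.7% |

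Over this range the artefact runs from 0.6 to 10.0 percentage points, against a design difference of 6.7 points.

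**4. The 50% rule (a follow-up share, not a change).** Rates again assumed.

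- 45% of starters meet it; joiners 20% of starters, 80% of whom meet it: (0.45 + 0.16)/1.2 = 50.8%.
- As above, with 10% of starters also withdrawn, none of whom would have met it: 0.61/1.1 = 55.5%.
- 40% of starters; 20% joiners at 60%: 0.52/1.2 = 43.3%, still a fail.

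Taking 134 starters at 45% (60.3 children), 20 leavers of whom 10% would have met the rule, and 20 joiners of whom 65% do:

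- joiners alone: (60.3 + 13)/154 = 47.6%, a fail;
- leavers alone: (60.3 − 2)/114 = 51.1%, a pass;
- both: 71.3/134 = 53.2%, a pass.

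In this example the leavers, not the joiners, carry the result over the line.

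**5. The 75% rule.** Rates assumed.

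- 70% of starters satisfied; 10% withdraw, three quarters of them dissatisfied: 0.675/0.9 = 75.0%.
- Adding 20% joiners at 90%: 0.855/1.1 = 77.7%.
- 65% of starters; 20% joiners at 90%; no withdrawals: 0.83/1.2 = 69.2%, still a fail.

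Either rule can flip when the starters' share is close to the threshold. Neither flips when it is further away and selection is moderate.

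**The case against.** The strongest reply is that the article does not prescribe an unpaired, all-available analysis. It leaves pairing, analysis sets and denominators unstated, and a condensed article may leave these to a fuller plan. The chi-square sentence concerns healthier-product share; for vegetables no test is named. This stands as far as it goes: a reader might infer that the plan has fixed an unpaired comparison of everyone present, and the text does not say so. It does fix open enrolment, a comparison across time and statements elsewhere that contradict open enrolment. It also acknowledges the missing baseline without drawing any consequence for the analysis.

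Further points on the other side are also correct:

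- The 50% and 75% rules are shares at follow-up. A reader might infer that they measure participation instead of change, but they were never measures of change. Late joiners eat the lunch and belong to the population research question 1 asks about.
- Late joiners need not all lack a baseline; the article says only that it can be missing.
- Withdrawal is from the study, which need not mean leaving the lunch. Children may bring an item from home and widely disliked products are replaced, so dislike need not lead to exit.
- That those who like the lunch join and those who dislike it leave is plausible but unsourced. Selective eaters might equally join late and lower the share.
- Counting every withdrawn child as a failure in the main analysis would treat exits for unrelated reasons as dislike. That exchanges a possible upward bias for a built-in downward one.

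None of these removes the case for making the time comparison within children measured at both ends.

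**Conclusion.** The point holds for the T0 to T1/T2 comparisons. With open enrolment, no comparison group for research question 1 and no restriction to children with a baseline, the analysis as described allows a change in who is measured to be read as a change in eating. The contradiction between Study design and Recruitment on consent and baseline is a matter of text and needs no assumption.

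The size cannot be determined from the documents. Under the assumed rates it ranges from negligible to larger than the effect the study is powered for. A direction favourable to the lunch is probable, but remains an inference. For the 50% and 75% rules the supported conclusion is narrower: whose intake and liking are counted is undefined, and this can matter near the threshold. The documents do not support saying that either rule will be passed through selection, or that late joiners should be excluded from describing how the lunch is eaten and liked.

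**What to change.** 1. Make the main T0 to T1 and T0 to T2 comparisons, for vegetables and for healthier-product share, within children who have a baseline and the relevant follow-up, using a paired or repeated-measures method. Membership is then the same at both ends, although the result describes children who stayed. Show an all-available analysis as sensitivity.
2. For the 50% and 75% rules, report the percentage for children enrolled at T0 and for late joiners separately. Add a sensitivity analysis that keeps withdrawn children in the denominator as not meeting the criterion.
3. Report the numbers joining and withdrawing by school.
4. Reconcile the Study design statements on consent and baseline with late enrolment in Recruitment.

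Cost: no new data are needed. The main time comparison will hold somewhat fewer children, and the success percentages may be lower. Because Study status says data collection is complete and analysis under way, the report should state when these definitions were set.
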